CHTC has been used as an HIV prevention intervention for heterosexual couples in Africa for over 20 years [14]. Labeled as a, “ *high leverage HIV prevention intervention* ” by the US Centers for Disease Control and Prevention (CDC) [15], CHTC is considered to be an effective approach to HIV prevention among male couples. The difference between CHTC and individual HIV testing and counseling is that both partners receive counseling and testing at the same time, and do so together [16]. During the CHTC session, the counselor learns about the couple’s relationship and provides tailored counseling and HIV prevention recommendations based on the characteristics of the couple’s relationship and their joint HIV status [16]. Through the adaptation of CHTC and the high acceptability among MSM [14,17], preliminary data from MSM in three US cities (Atlanta, Chicago, Seattle) demonstrates the readiness of US MSM to receive and use CHTC [18,19]. Preliminary findings also suggest that male couples receiving CHTC, in which intimate partner violence (IPV) is not already present, do not report increased levels of IPV or relationship dissolution [20]. CHTC is now considered by the CDC to be an effective public health strategy, and is currently being implemented in over 40 US states [16,21].

A critical aspect of CHTC involves discussing a couple’s sexual agreement. Sexual agreements are common among male couples and refer to mutually understood rules between two partners that describe the kinds of sexual behavior that is allowed within and outside of the relationship [4,22-29]. In CHTC, male couples discuss their sexual agreements, role-play with the counselor about how they would communicate about a breach in the sexual agreement, and develop an HIV prevention plan based on their agreement and couple sero-status. Research regarding male couples’ agreements has demonstrated that men are less likely to practice condomless anal intercourse (CAI) with both primary and outside partners if they value and commit to their agreement and perceive their main partner to be dependable and invested in the relationship [28,30-32]. Promoting positive relationship dynamics has the potential to reduce couples’ risk for HIV because higher trust, communication, commitment, and social support are associated with lower odds of breaking a sexual agreement, which can ultimately reduce unique HIV risks (eg, CAI) for the couple [3].

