### Dyadic Characteristics: Analysis of the Scale Data Over Time

Repeated-measures analyses using mixed linear models will be performed for scale data. These analyses will include participant-level characteristics and couple-level variation or clustering. Participants will be nested within couples with the participant as the experimental unit. Repeated-measures analyses for each scale will be analyzed with a means model with SAS Proc Mixed providing separate estimates of the means by time on study and treatment group. An unstructured variance-covariance form among the repeated measurements will be assumed for each outcome, and estimates of the standard errors of parameters will be used to perform statistical tests and construct 95% confidence intervals. T-tests will be used to compare the pairwise differences between the model-based treatment means (least-squares means) at each time point. Statistical tests will be 2-sided. The model-based means are unbiased with unbalanced and missing data if missing data are noninformative (missing at random). A dropout process is assumed to be missing at random if, conditional on the observed data, the dropout is independent of the unobserved measurements.

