The analysis will also examine conceptual mediators and epidemiologically identified moderators. If the Stronger Together intervention works to increase viral suppression and number of participants reporting full engagement in care among the intervention sample in significantly greater magnitude than the comparison condition, we will assess the extent to which this relationship works through several possible mediators, including dyadic factors and relationship functioning (ie, communication). For mediation analyses, we will employ MEDIATE procedures. MEDIATE estimates the total, direct, and indirect effects of causal variable(s) on the outcome variable through a proposed mediator variable or set of mediator variables. For effect modification (moderation) analyses, we will add interaction terms one-by-one for the intervention condition and the potential moderators (eg, age, race/ethnicity, and psychosocial factors such as depression and length of relationship). Significant or large interaction terms would suggest that the effects of the intervention differ for different subgroups, as defined by the moderators.

The analysis will also examine HIV sero-conversion among HIV-negative partners and syphilis as secondary outcomes: the prevalence and 24-month cumulative incidence of HIV and syphilis will be examined in aggregate and then by study arm. During the interim assessment visits (that occur before month 12 and then again before month 24) we will collect information on STI testing/diagnosis/treatment that participants received elsewhere since their last study assessment visit. These data will be used to adjust analyses. Using Cox proportional hazard regression models, we will assess if intervention status results in decreased odds (hazard ratio) of HIV and STI infection, separately, over the 24-month period.

The safety of the intervention at the individual level will be assessed by examining reported IPV within the relationship and relationship dissolution. Prevalence of each individual adverse outcome or any adverse outcome will be calculated, and prevalence of outcomes will be compared in the control and intervention groups using Chi-square tests or Fischer’s exact tests, as appropriate.

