### Sample Size

Estimating 80% retention, we propose to enroll a sample of 165 male sero-discordant couples. The primary outcomes are engagement in HIV care and viral suppression. A sample of 165 sero-discordant couples provides statistical power (with 95% confidence and 80% power) to detect scientifically significant relative differences of 15%, 20%, and 25% in each of these outcomes between the two study arms. Additional health-enhancing behaviors include recent sexual risk-taking; using the data from our previous RCT of CHTC, this sample of 165 sero-discordant couples provides statistical power to identify significant differences in sexual risk-taking between the two arms. Using the methods described by Rosner for sample size estimation for longitudinal studies [67], a sample size of 75 couples in each group will ensure statistical power (using a two-sided two-sample t-test) to identify differences in the dyadic scale constructs between arms. As secondary outcomes, the study will examine sero-conversion and syphilis incidence between the two arms, although the power is insufficient to detect significance differences between the study arms.

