## Results

Stronger Together was launched in August 2014. To date, 160 couples (97% of the target enrollment) have been enrolled and randomized. The average retention rate across the surveys is 95%: current retention at 24 months is >90% across sites. Relationship dissolution has been relatively low, with only 13 couples breaking up during the RCT (13/160, 8%). Of the 13 couples who have broken up, 10 of the 13 (77%) HIV-positive partners have been retained in the cohort; none of these HIV-positive partners have enrolled new partners in the RCT.

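### The between-arm safety comparison rests on tests for difference alone, which at this size miss a doubling of break-ups about 65–79% of the time, so a non-significant result cannot support a statement of no increased harm

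*Protocol article*

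**What the plan says.** The safety paragraph closes the section *Incidence of Aggregate 'Sex at Risk' Within Partnerships*. It says "The safety of the intervention at the individual level will be assessed by examining reported IPV within the relationship and relationship dissolution". Prevalence is to be computed for each adverse outcome and for any adverse outcome, and "prevalence of outcomes will be compared in the control and intervention groups using Chi-square tests or Fischer’s exact tests, as appropriate". No interval estimate and no statement of power accompanies this.

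Four other places bear on it:

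- *Sample Size* bases the 165 couples on care engagement and viral suppression, "with 95% confidence and 80% power". For sero-conversion and syphilis it adds "although the power is insufficient to detect significance differences between the study arms". It says nothing about power for IPV or dissolution.
- The section on dyadic scale data and the section on at-risk sex both commit to 95% confidence intervals. The safety paragraph does not.
- *Results* reports 13 break-ups among 160 randomized couples, arms pooled, with follow-up still running.
- The *Introduction* describes preliminary couples-testing findings in which couples without existing IPV "do not report increased levels of IPV or relationship dissolution".

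**The concern.** A test for difference limits the chance of declaring harm when there is none. In a safety comparison the more costly error is to miss harm that is present, and nothing in the stated method controls that error or shows its size. With few events and a sample chosen for other outcomes, a non-significant result is likely whether or not the intervention increases break-ups.

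The question matters here because the counseling deals directly with sexual agreements and with how a breach would be discussed, and IPV and dissolution are the two named safety outcomes. If the trial reports only two prevalences and a p-value, the reader cannot see how large an excess remains compatible with the data.

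**Working it through.** **Inputs**

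- Planned couples: 165 (*Sample Size*), allocated about 1:1 by odd or even random number (*Randomization*). 165/2 = 82.5, taken as 82 per arm. At the planned 80% retention, 165 × 0.80 = 132, or 66 per arm. *Results* gives 160 randomized, about 80 per arm.
- Break-up risk: 13/160 = 8.1%, which reproduces the stated 8%. Using this pooled interim figure as the control risk is an assumption.
- Test level: 5%, two-sided. The article gives 95% confidence for the primary outcomes and says "Statistical tests will be 2-sided" for the scale data. Carrying these over to safety is an assumption.
- Unit for break-up: one yes/no outcome per couple.

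**Approximate check, 8% vs 16%**

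Miss rate = 1 − Φ[(Δ − 1.96·SE₀)/SE₁], with Δ = 0.08, mean risk 0.12, SE₀ = √(2 × 0.12 × 0.88/n) and SE₁ = √((0.08 × 0.92 + 0.16 × 0.84)/n).

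- n = 82: SE₀ = 0.0508, SE₁ = 0.0504. (0.08 − 0.0995)/0.0504 = −0.39, so the miss rate is 65%.
- n = 66: SE₀ = 0.0566, SE₁ = 0.0561. (0.08 − 0.1109)/0.0561 = −0.55, so the miss rate is 71%.

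**Exact check**

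I enumerated two independent binomials and counted the probability that the test is not significant in the direction of harm. The Chi-square test is uncorrected.

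| Control vs intervention | n per arm | Chi-square | Fisher |
|---|---|---|---|
| 8% vs 16% | 82 | 65% | 72% |
| 8% vs 16% | 66 | 71% | 79% |
| 8% vs 24% | 82 | 18% | 24% |
| 8% vs 24% | 66 | 28% | 35% |
| 10% vs 20% | 82 | 57% | 64% |
| 10% vs 20% | 66 | 64% | 72% |
| 15% vs 30% | 82 | 36% | 43% |
| 15% vs 30% | 66 | 45% | 53% |

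If 8.1% is instead the average of two arms that already differ twofold (5.4% vs 10.8%), the miss rate is 77–84% at 80 per arm and 79–88% at 66. About 254 couples per arm would be needed for 80% power to detect a doubling from 8.1%.

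**What an interval would show**

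- Suppose 7/82 (8.5%) break up in control and 15/82 (18.3%) in intervention. Chi-square gives p = 0.067 and Fisher p = 0.107, both non-significant. The difference is 9.8 points with SE = √(0.0854 × 0.9146/82 + 0.1829 × 0.8171/82) = 0.0527. The 95% interval is 9.8 ± 10.3, or −0.6 to 20.1 points.
- If both arms show 8%, the half-width is 1.96 × √(2 × 0.08 × 0.92/n): 8.3 points at n = 82 and 9.3 at n = 66.
- If the 13 break-ups split 6 (control) and 7 (intervention) with 80 per arm, the 95% interval for the risk ratio is about 0.43 to 3.2. Near-equal counts would not exclude a doubling.

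**IPV**

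The article gives no IPV rate, so any figure is conditional. It places the safety assessment at the individual level and surveys both partners, so the unit may be the person. If partners' reports were independent, 164 per arm would give Chi-square miss rates for a doubling of 60%, 27% and 9% at control risks of 5%, 10% and 15%. At couple level with 82 per arm the figures are 79%, 57% and 36%. Because partners' reports are correlated, the truth should lie between the two sets.

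**The case against.** A reader might infer that a non-significant test will be declared proof of safety. The documents do not support that. The safety paragraph sets no decision rule, and the sentence in the *Introduction* describes earlier findings, not a criterion for this trial.

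A second tempting reading is that safety is watched only through these tests. That is also too strong: a Data Safety Monitoring Board meets annually, recent IPV is an exclusion at entry, and couples receive bi-monthly check-in calls. The point concerns the final between-arm comparison only.

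The strongest objection is that intervals, margins and power notes for safety are details a journal article may leave to a full protocol or analysis plan not shown here. Naming a test does not rule out an interval, and the planned prevalences by arm would allow one to be computed. This stands for a formal margin, whose absence is no fault. It carries less weight for the method itself: the article does state how the arms will be compared on safety, names only a test for difference, and elsewhere specifies intervals and a low-power caveat.

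The objection on inputs also stands in part. The 8% is interim and pooled, reported 24-month retention is above 90%, which makes 66 per arm pessimistic, and the miss rate falls if the final control risk is higher. A claim that a doubling of IPV would most likely be missed does not hold in general, because no rate is given and the unit may be the individual.

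**Conclusion.** The point holds in a limited form. As stated, the between-arm safety comparison relies on Chi-square or Fisher's exact tests. With 66 to 82 couples per arm, a control break-up risk of 8% and a two-sided 5% level, these miss a doubling of break-ups about 65–79% of the time. At a control risk of 15% the figure is about 36–53%. A non-significant result therefore cannot carry a statement of no increased harm.

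The control risk, the test level and the couple as unit are assumptions. Nothing firm can be said about the size of the problem for IPV. The defect is a method poorly suited to the question, together with a power caveat applied to some low-powered outcomes and not to these. It should be changed, but it does not affect the primary analysis.

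**What to change.** In the safety paragraph, make the primary safety summary the between-arm risk difference, with the risk ratio beside it, each with a 95% confidence interval, for dissolution, IPV and the any-adverse-outcome composite. The tests may stay as supplementary results. State the unit of analysis for IPV. If it is the individual, use a method that allows for correlation within couples.

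Add one sentence that a non-significant difference is not evidence of safety, and extend the insufficient-power statement in *Sample Size* to these outcomes. The investigators may also fix in advance, with the Data Safety Monitoring Board, the largest excess that the upper bound should exclude, but this is optional.

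The cost is a few sentences and a small number of intervals, with no new data or participants. The downside is that, with half-widths of about 8 to 9 points even when both arms show 8%, safety will probably have to be reported as inconclusive for moderate harms.

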### Incentives

Individual participants receive US $50 for completing each study visit; this includes baseline, Partner STEPS sessions, and all four-to-six follow-up visits, depending on the study arm. If both members of the couple complete all visits, the total incentive amount is US $500 per couple ($250 per individual participant) in the control and US $700 per couple ($250-350 per individual participant) in the intervention arm.

### Sample Size

Estimating 80% retention, we propose to enroll a sample of 165 male sero-discordant couples. The primary outcomes are engagement in HIV care and viral suppression. A sample of 165 sero-discordant couples provides statistical power (with 95% confidence and 80% power) to detect scientifically significant relative differences of 15%, 20%, and 25% in each of these outcomes between the two study arms. Additional health-enhancing behaviors include recent sexual risk-taking; using the data from our previous RCT of CHTC, this sample of 165 sero-discordant couples provides statistical power to identify significant differences in sexual risk-taking between the two arms. Using the methods described by Rosner for sample size estimation for longitudinal studies [67], a sample size of 75 couples in each group will ensure statistical power (using a two-sided two-sample t-test) to identify differences in the dyadic scale constructs between arms. As secondary outcomes, the study will examine sero-conversion and syphilis incidence between the two arms, although the power is insufficient to detect significance differences between the study arms.

### Trial Registration, Ethics, Consent, and Institutional Board Approval

The research and ethics presented in this study have been reviewed and approved by the Institutional Review Boards (IRBs) of Emory University (IRB #00065111), Lurie Children’s (IRB #2014-15896) and The Fenway Institute (IRB #FWA00000145), in addition to a Data Safety Monitoring Board that meets annually. The study is also registered on ClinicalTrials.gov (NCT01772992).

## Results

Stronger Together was launched in August 2014. To date, 160 couples (97% of the target enrollment) have been enrolled and randomized. The average retention rate across the surveys is 95%: current retention at 24 months is >90% across sites. Relationship dissolution has been relatively low, with only 13 couples breaking up during the RCT (13/160, 8%). Of the 13 couples who have broken up, 10 of the 13 (77%) HIV-positive partners have been retained in the cohort; none of these HIV-positive partners have enrolled new partners in the RCT.

## Discussion

Dyadic interventions provide an opportunity for male sero-discordant couples to learn the skills necessary to work together to manage HIV in their relationships. By developing tailored prevention plans in CHTC and developing problem solving skills in Partner STEPS, the intervention offers a unique opportunity for sero-discordant couples to support each other towards common HIV management goals. The intervention tested in this protocol builds off the current success of CHTC. The current intervention extends the focus of dyadic interventions for male couples across the continuum of HIV care, allowing male couples to develop the skills necessary to support active and successful engagement of HIV care. The intervention has the potential to fill a critical gap in efficacious interventions for male sero-discordant couples who, despite evidence of high rates of transmission within partnerships, have been largely ignored by HIV research and programming.

## Abbreviations

ACTG: AIDS Clinical Trial Group
AIDS: acquired immune deficiency syndrome
ART: antiretroviral therapy
CAI: condomless anal intercourse
CHTC: couples’ HIV testing and counseling
CTR: counseling, testing, and referral
GEE: generalized estimating equations
GLM: generalized linear model
HIV: human immunodeficiency virus
IPV: intimate partner violence
IRB: Institutional Review Board
IRR: incidence rate ratio
LGBT: lesbian, gay, bisexual, and transgender
MSM: men who have sex with men
NHBS: National HIV Behavioral Surveillance
PrEP: preexposure prophylaxis
RCT: randomized controlled trial
STEPS: Strategies to Enhance Problem-solving Skills
STI: sexually transmitted infection
URL: Uniform Resource Locator
